#### **11.2.2. Number of stools**

Number of stools per day will be assessed and reported at each visit. The responses to the average number of bowel movements per day will be coded as: 0=0, 1=1, 2=2, 3=3, 4=4, 5=5, 6=6, 7=7, 8=8, 9=9, and 10=10+. The score for number of bowel movements over the 16-week study will be analyzed as described in section 11.2.

#### **11.2.3. Stool consistency**

Stool consistency in the past 24 hours will be assessed and reported at each visit. The responses to the consistency of the bowel movement will be coded as: 1=Hard, 2=Formed Soft, 3=Mushy Soft, 4=Runny Soft, 5=Watery. The score for stool consistency over the 16-week study will be analyzed as described in section 11.2.

#### **11.2.4. Fussiness**

Two separate questions for fussiness will be assessed and reported at each visit. Fussiness in the past 24 hours will be coded as: 0=Not at all fussy, 1=Slightly fussy, 2=Moderately fussy, 3=Very fussy, and 4=Extremely fussy. Over the past 24 hours, fussiness compared to normal will be coded as: 0=Less fussy than normal, 1=About the same level of fussiness as always, and 2=More fussy than normal. Each score for fussiness over the 16-week study will be analyzed as described in section 11.2.

#### **11.2.5. Amount of gas**

Two separate questions for gassiness, and amount of gas in the past 24 hours will be assessed and reported separately at each visit. Gas over the past 24 hours will be coded

as: 0=None at all, 1=Slight amount of gas, 2=Moderate amount of gas, and 3=Excessive amount of gas. Over the past 24 hours, gassiness compared to normal will be coded as: 0=Less gas than normal, 1=About the same amount of gas as normal, and 2=More gas than normal. Each score for gassiness over the 16-week study will be analyzed as described in section 11.2.

#### 11.2.6. Infant Characteristics Questionnaire (ICQ)

The Infant Characteristics Questionnaire (ICQ) was administered at visits 1, 2, 3, 5, 7, and 9. The ICQ (Appendix A) was developed as a short, factor-analytic screening device for difficultness (Bates et al., 1979). The data from the 24-item questionnaire will be summarized into four subscales: Fussy-difficult, Unadaptable, Dull, and Unpredictable. Based on the examination of the factor structure of the items, the authors of the ICQ composed scales using only the discriminating items for use with their normative sample. These scales are composed as follows:

- Fussy/Difficult: Items 1, 5, 6, 13, 22, and 24
- Unadaptable: Items 9, 10, 11, and 20
- Dull: Items 15 (reverse-coded), 16, and 23
- Unpredictable: Items 2, 3, and 4

The sum of the responses for each of the items above comprise the score for each scale. A response for each item is required to calculate a sum score, otherwise the sum score will be set to missing. Higher scores indicate a more difficult temperament. ICQ scales will be summarized by study visits at study sites. Study visits are planned to occur every 15 or 30 (+/- 3) days. A window will be applied to each visit to ensure that subjects are compared at the same formula duration.

| Analysis Visit | Target Day | Window    |
|----------------|------------|-----------|
| 1              | 0          | N/A       |
| 2              | 15         | 8 – 22    |
| 3              | 30         | 23 – 44   |
| 5              | 60         | 45 – 74   |
| 7              | 90         | 75 – 104  |
| 9              | 120        | 105 – 134 |

If more than 1 visit falls within a window, then the visit closest to the target day will be used in the analysis. If more than one visit falls within a window and they are the same distance to the target day, then the latest visit will be used in the analysis. Unscheduled assessments will be assigned to the associated visit based on date and time of assessment.

The scores of the four subscales will be summarized separately by formula group with descriptive statistics at each of the 6 visits. The test for treatment effect of each score over the 16-week study will have the following hypotheses:

H0: There is no difference between the formula groups.

H1: There is a difference between the formula groups.

Formula groups will be compared using a MMRM with sex, age at enrollment, baseline value, formula, pooled site, visit, formula by pooled site interaction, and formula by visit interaction as factors. The covariance matrix will be chosen based on the AIC criteria to choose the covariance matrix that best fits the model. In addition, the formula effect by visit will be summarized. An alpha level of 0.05 will be used to test the formula effect. 95% confidence intervals and p-values will be reported on the difference of least square means for comparison of formula groups at each visit.

The items which are included in the questionnaire but not included in scales above will be summarized individually with descriptive statistics by visit and formula group.

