## ● Appendix A: Infant Characteristics Questionnaire

On the following questions, please circle the number that is most typical of your baby. “About average” means how you think the typical baby would be scored. Put NA next to any item that does not apply to your baby. For example, if your baby has not had solid food yet, you would mark the item regarding his/her reaction to solid food as NA.

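### One NA item voids an ICQ subscale, and a void Visit 1 score drops the infant from that subscale's MMRM; the Unadaptable scale is the one plausibly exposed

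*Supplement*

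**What the plan says.** SAP V4 section 11.2.6 builds four subscales by summing items. The one that matters most here is "Unadaptable: Items 9, 10, 11, and 20". Of the rest, the Fussy/Difficult scale has six items (numbers 1, 5, 6, 13, 22, 24), while Dull (15 with its coding reversed, 16, 23) and Unpredictable (2 to 4) have three each. The completeness rule is "A response for each item is required to calculate a sum score, otherwise the sum score will be set to missing". There is no minimum number of items, no prorating, and no separate rule for NA.

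The form in Appendix A tells parents "Put NA next to any item that does not apply to your baby". Its only illustration is item 8, on first solid food.

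For the comparison, section 11.2.6 states: "Formula groups will be compared using a MMRM with sex, age at enrollment, baseline value, formula, pooled site, visit", followed by the two formula interactions. Section 6.3 defines baseline as the last available value before the first study feeding. Section 6.4 plans no imputation in general. The multiple imputation in section 9.1.1 covers only the primary endpoint. ICQ scales form part of the secondary safety objective (section 2.2.5).

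**The concern.** The form invites an answer that the scoring rule treats as voiding the subscale. This matters most at Visit 1, where protocol 5.2 section 7.1 requires infants to be no older than 14 days. Items 9, 10, 11 and 20 ask how the baby reacts to new people, to new places, to things over time, and to upsets in routine such as outings. A parent of a newborn may reasonably find that some of these do not yet apply. Item 11 also refers back to items 7 to 10, which include item 8 on solid food, the form's own NA example.

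A void score at a later visit loses that visit only. A void Visit 1 score loses more, because it is also a covariate for every later visit. Answers already collected for a safety comparison would be discarded, and the modelled comparison would be confined to infants for whom every item of the scale already applied in the first two weeks.

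**Working it through.** **Step 1: is there a fallback baseline?** The ICQ is given at Visits 1, 2, 3, 5, 7 and 9. Only Visit 1 (Day 0) can precede study feeding, so the definition in section 6.3 has nothing earlier to draw on. If the Visit 1 subscale is void, the baseline is missing.

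**Step 2: what does the model do with it?** The SAP does not say in words that the infant is removed. Removal follows from a missing covariate, no imputation, and the usual behaviour of a standard mixed model, which drops every record lacking a covariate. The multinomial alternative in section 11.2 also includes the baseline value, so it offers no escape.

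A simulation of 225 infants (139 Brand + 86 BBN-102, the planned enrolment in section 5) illustrates this with a four-item scale and a 5% NA rate per item at Visit 1 only. In the draw, 43 infants lacked the baseline score and 182 entered the model. All 43 × 5 = 215 post-baseline scores of those infants were lost, although every one had been observed.

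**Step 3: how large could the loss be?** The plan states no figure to reproduce, and no NA rate for any item. Take an assumed rate p per item, independent between items. For a scale of k items, the chance that it is void at Visit 1 is 1 − (1 − p)^k. For Unadaptable, k = 4:

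| p | 1 − (1 − p)^4 | Expected of 225 | Expected of 86 BBN-102 |
|---|---|---|---|
| 2% | 1 − 0.98^4 = 7.8% | 17.5 | 6.7 |
| 5% | 1 − 0.95^4 = 18.5% | 41.7 | 16.0 |
| 10% | 1 − 0.90^4 = 34.4% | 77.4 | 29.6 |

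The counts use planned enrolment, before attrition. NAs that cluster within the same infants would give smaller losses at the same p.

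**Step 4: what would prorating recover?** If three of four answered items suffice, the scale is void only with two or more NAs: 1 − (1 − p)^4 − 4p(1 − p)^3.

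- p = 2%: 1 − 0.9224 − 0.0753 = 0.2%
- p = 5%: 1 − 0.8145 − 0.1715 = 1.4%
- p = 10%: 1 − 0.6561 − 0.2916 = 5.2%

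Under the same assumptions, most of the Visit 1 loss disappears.

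**The case against.** The size is wholly assumed. The form's only NA example is item 8, which belongs to no subscale, so that answer alone voids nothing. This stands, and is why the loss is shown as a range.

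Three stronger readings are tempting, and the documents support none of them.

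- *The infant is lost to the ICQ analysis altogether.* Each subscale has its own model, so a void Unadaptable score leaves the other three alone. Later scores still appear in the by-visit descriptive statistics, which need no baseline.
- *All four scales are at similar risk, and the six-item scale most of all.* With equal p, Fussy/Difficult would lose 26.5% at 5%. But its items concern soothing, crying, mood and overall difficulty, which apply to any newborn. So do the Unpredictable items on sleep, hunger and reasons for crying. Dull items 16 and 23 have low-end anchors that a parent can circle in place of NA.
- *The Day 120 comparison loses everyone with a void score at either Visit 1 or Day 120.* That gives 1 − (1 − p)^8 = 15%, 34% and 57% at 2%, 5% and 10%. It carries a newborn's NA rate forward to an age at which its reason has largely gone. It also counts as lost the infants void only at Day 120, who remain in the MMRM through their other visits.

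Complete-item scoring is also a defensible conservative choice, and nothing in the documents endorses a particular prorating threshold. Visit 1 precedes study feeding, so an NA there cannot be caused by the formula; the likely cost is precision and generalisability. Fussiness is measured separately at every visit (section 11.2.4). These points limit the importance of the matter. They do not remove the conflict between form and scoring rule, or supply a rule for a missing baseline.

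**Conclusion.** The point holds, as a cheap improvement to a secondary safety analysis. The form and the scoring rule conflict, and a void Visit 1 score takes an infant's complete later scores out of that subscale's MMRM. Only the Unadaptable scale is plausibly exposed to a material degree. Its loss from Visit 1 alone would be 7.8%, 18.5% or 34.4% of infants if NAs are independent at 2%, 5% or 10% per item, and less if they cluster. Those rates are assumptions, and removal is inferred from the specified model rather than stated in the SAP. The weight-gain primary endpoint is unaffected.

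**What to change.** 1. **Scoring.** Say in section 11.2.6 how NA is handled. Score a subscale as the mean of the answered items times the number of items when more than half are answered: at least 4 of 6, 3 of 4, or 2 of 3. Keep complete-item scoring as a sensitivity analysis.
2. **Visit 1 score still missing.** Add a supportive analysis that keeps the infant in, for example by fitting Visit 1 as an outcome rather than a covariate.
3. **Assumption to declare.** A common Visit 1 mean across groups normally rests on concurrent randomisation. Here about 129 of the 139 Brand infants come from phase one, and section 9.1.2 already treats similarity across enrolment periods as something to assess. State the common mean as an assumption, and repeat the model with Visit 1 means free to differ by group or phase.
4. **Reporting.** Tabulate NA counts by item, visit and group, so that the actual loss is visible.

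The cost is SAP wording, one scoring macro and one extra model, with no new data. Prorating has a real but small price: it assumes that the answered items represent the unanswered ones, which the complete-item sensitivity analysis helps to check.

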### **11.3. Physical Examination**

Physical examination results will be listed by subject. No summary tables of physical examination are planned.

### **11.4. Prior and Concomitant Medications**

At each study visit, site personnel will interview parent(s)/guardian(s) to obtain information about all concomitant therapy that was administered since the previous study visit. Concomitant medications include prescription medications, over-the-counter medications, and herbal supplements. This information will be recorded in the infant's medical record.

Any medications or therapy administered and discontinued before the first feeding of randomized formula will be considered as prior medications. Concomitant medications (medications present while consuming randomized formula during the study period) will be recorded throughout the study and at early discontinuation. Prior and concomitant medication verbatim terms captured via the EDC system will be mapped to Anatomical/Therapeutic/Chemical (ATC) class and Preferred Terms using the World Health Organization (WHO) Drug Dictionary, B3 September 2020 version.

Concomitant medications will be summarized for each formula group by WHO ATC class and preferred term. These summaries will present the number and percent of infants using each medication. Subjects may have more than one medication per ATC

class and preferred name. At each level of subject summarization, a subject is counted once if one or more medications at that level is reported for the subject. Each summary will be ordered by descending order of incidence of ATC class and preferred term.

Prior medications will be listed by subject.

## **12. Planned Tables, Figures, and Listings**

A table of contents for the tables, listings, and figures will be presented in a separate document as the list of summaries or numbering may change after finalization of this document. If additional summaries are added that are not described in this document, then this SAP will be amended, or an addendum will be created.

## ● Appendix A: Infant Characteristics Questionnaire

On the following questions, please circle the number that is most typical of your baby. “About average” means how you think the typical baby would be scored. Put NA next to any item that does not apply to your baby. For example, if your baby has not had solid food yet, you would mark the item regarding his/her reaction to solid food as NA.

### 1. How easy or difficult is it for you to calm or soothe your baby when he/she is upset?

| 1         | 2 | 3 | 4                        | 5 | 6 | 7         |
|-----------|---|---|--------------------------|---|---|-----------|
| Very easy |   |   | About
ave
rag
e |   |   | Difficult |

### 2. How easy or difficult is it for you to predict when your baby will go to sleep and wake up?

| 1         | 2 | 3 | 4                        | 5 | 6 | 7         |
|-----------|---|---|--------------------------|---|---|-----------|
| Very easy |   |   | About
ave
rag
e |   |   | Difficult |

### 3. How easy or difficult is it for you to predict when your baby will become hungry?

| 1         | 2 | 3 | 4                        | 5 | 6 | 7         |
|-----------|---|---|--------------------------|---|---|-----------|
| Very easy |   |   | About
ave
rag
e |   |   | Difficult |

### 4. How easy or difficult is it for you to know what’s bothering your baby when he/she cries or fusses?

| 1         | 2 | 3 | 4                        | 5 | 6 | 7         |
|-----------|---|---|--------------------------|---|---|-----------|
| Very easy |   |   | About
ave
rag
e |   |   | Difficult |

### 5. How many times per day, on the average, does your baby get fussy and irritable--for either short or long periods of time?

| 1 | 2 | 3 | 4 | 5 | 6 | 7 |
|---|---|---|---|---|---|---|
|---|---|---|---|---|---|---|

|       |                   |                   |                   |                   |                     |              |
|-------|-------------------|-------------------|-------------------|-------------------|---------------------|--------------|
| Never | 1-2 times per day | 3-4 times per day | 5-6 times per day | 7-9 times per day | 10-14 times per day | More than 15 |
|-------|-------------------|-------------------|-------------------|-------------------|---------------------|--------------|

**6. How much does your baby cry and fuss in general?**

|                                              |   |                                                   |   |   |   |                                        |
|----------------------------------------------|---|---------------------------------------------------|---|---|---|----------------------------------------|
| 1                                            | 2 | 3                                                 | 4 | 5 | 6 | 7                                      |
| Very little; much less than the average baby |   | Average amount; about as much as the average baby |   |   |   | A lot; much more than the average baby |

**7. How did your baby respond to his/her first bath?**

|                           |   |                               |   |   |   |                           |
|---------------------------|---|-------------------------------|---|---|---|---------------------------|
| 1                         | 2 | 3                             | 4 | 5 | 6 | 7                         |
| Very well-- baby loved it |   | Neither liked nor disliked it |   |   |   | Terribly-- didn't like it |

**8. How did your baby respond to his/her first solid food?**

|                                       |   |                               |   |   |                                         |   |
|---------------------------------------|---|-------------------------------|---|---|-----------------------------------------|---|
| 1                                     | 2 | 3                             | 4 | 5 | 6                                       | 7 |
| Very favorably-- liked it immediately |   | Neither liked nor disliked it |   |   | Very negatively--did not like it at all |   |

**9. How does your baby typically respond to a new person?**

|                                  |   |                                        |   |   |                                            |   |
|----------------------------------|---|----------------------------------------|---|---|--------------------------------------------|---|
| 1                                | 2 | 3                                      | 4 | 5 | 6                                          | 7 |
| Almost always responds favorably |   | Responds favorably about half the time |   |   | Almost always responds negatively at first |   |

**10. How does your baby typically respond to being in a new place?**

|                                  |   |                                        |   |   |                                            |   |
|----------------------------------|---|----------------------------------------|---|---|--------------------------------------------|---|
| 1                                | 2 | 3                                      | 4 | 5 | 6                                          | 7 |
| Almost always responds favorably |   | Responds favorably about half the time |   |   | Almost always responds negatively at first |   |

**11. How well does your baby adapt to things (such as in items 7-10) eventually?**

|                                       |   |                                       |   |   |                                      |   |
|---------------------------------------|---|---------------------------------------|---|---|--------------------------------------|---|
| 1                                     | 2 | 3                                     | 4 | 5 | 6                                    | 7 |
| Very well, always likes it eventually |   | Ends up liking it about half the time |   |   | Almost always dislikes it in the end |   |

**12. How easily does your infant get upset?**

|   |   |   |   |   |   |   |
|---|---|---|---|---|---|---|
| 1 | 2 | 3 | 4 | 5 | 6 | 7 |
|---|---|---|---|---|---|---|

|                                                                  |               |                                                                    |
|------------------------------------------------------------------|---------------|--------------------------------------------------------------------|
| Very hard to upset--
even by things that
upset most babies | About average | Very easily upset by
things that wouldn't
bother most babies |
|------------------------------------------------------------------|---------------|--------------------------------------------------------------------|

**13. When your baby gets upset (e.g., before feeding, during diapering, etc.), how vigorously or loudly does he/she cry and fuss?**

|                                    |   |                                   |   |   |                                               |   |
|------------------------------------|---|-----------------------------------|---|---|-----------------------------------------------|---|
| 1                                  | 2 | 3                                 | 4 | 5 | 6                                             | 7 |
| Very mild intensity
or loudness |   | Moderate intensity
or loudness |   |   | Very loud or
intense, really
cuts loose |   |

**14. How does your baby react when you are dressing him/her?**

|                     |   |                                |   |   |                        |   |
|---------------------|---|--------------------------------|---|---|------------------------|---|
| 1                   | 2 | 3                              | 4 | 5 | 6                      | 7 |
| Very well--likes it |   | About average--doesn't mind it |   |   | Doesn't like it at all |   |

**15. How active is your baby in general?**

|                     |   |         |   |   |                          |   |
|---------------------|---|---------|---|---|--------------------------|---|
| 1                   | 2 | 3       | 4 | 5 | 6                        | 7 |
| Very calm and quiet |   | Average |   |   | Very active and vigorous |   |

**16. How much does your baby smile and make happy sounds?**

|                                           |   |                   |   |   |                                          |   |
|-------------------------------------------|---|-------------------|---|---|------------------------------------------|---|
| 1                                         | 2 | 3                 | 4 | 5 | 6                                        | 7 |
| A great deal, much more than most infants |   | An average amount |   |   | Very little, much less than most infants |   |

